5.2.3.2 Foot and ankle exercise programme

The foot and ankle exercise programme, which is currently being used by our Australian collaborator, will be piloted within a UK context and adapted to make it suitable for a UK setting. The exercise programme aims to stretch and strengthen the muscles of the foot and ankle. A summary of the individual exercises which will be used in the home based exercise programme is given in table 1. All exercises will be demonstrated and the patient assessed for competence at the baseline and follow-up appointments. Any patient specific advice will be given with opportunity to contact the podiatrist anytime during the course of the study.

Table 1 Description of home based foot and ankle exercises

| **Activity** | **Description** | **Dosage** | **Increments** |
| --- | --- | --- | --- |
| Ankle range of motion | Sitting with knee extended. Rotate foot in clockwise direction and then anti-clockwise. | 1x10 repetitions for each foot in each direction. | None. |
| Ankle inversion strength | Sitting upright, hip and ankle at 90º. Invert foot against resistive exercise band held by the hand on the same side. | 3x10 repetitions for each foot. | Increase resistance strength of resistive exercise band. |
| Ankle eversion strength | Sitting upright, hip and ankle at 90º. Evert foot against resistive exercise band anchored by the opposing foot. | 3x10 repetitions for each foot. | Increase resistance strength of resistive exercise band. |
| Ankle dorsiflexion strength | Sitting, hip and ankle at 90º.  Dorsiflex both feet to end range of motion and hold. | Hold feet in dorsiflexion for 3x10 seconds. | Increase repetitions up to maximum of 10. |
| Intrinsic strengthening, toe plantarflexion strength and toe stretch | Sitting, hip and ankle at 90 º.  1) Use the therapy ball under the toes to stretch the toes with the foot plantargrade and then curl and point the toes up and over the ball. 2)With the heel on the floor, attempt to pick up the ball with the toes. | 3 x10 repetitions for each exercise both feet. Have a 30 sec break between each repetition | Increase up to a maximum of 50 repetitions. |
| Ankle plantarflexion strength | From standing, rise up onto toes of both feet and then lower back down. | 3x10 repetitions. | Increase repetitions up to maximum of 50. |
| Calf stretch | Sitting, hip at 90 º placing theraband around ball of foot, knee is extended, pull therabands towards body. | Hold stretch for 3x20 seconds on each leg. | Increase forward lean to increase stretch as required. |
| Proprioception/balance training | From standing and holding on to a chair/wall for support, stand on one leg. Repeat on the other side | Hold for 30 seconds.  Repeat 3 repetitions. | Increase slowly to hold for 1 min per repetition.  If competent, rise up on to toes on the one supporting leg: 3 x 10 repetitions. |

5.2.3.3 Footwear assessment and shoe provision

We wish to explore the feasibility of making a footwear assessment, providing footwear advice, provision of the footwear voucher and likely purchase of new footwear. In addition to this we will look at the time taken to explain the exercise programme and fit the device in order to develop the package of care for the main trial.

During this phase of the study we will develop a podiatrist training programme and pilot the patient self-report questionnaires and calendars.

5.2.4.1 Data collection and analysis for quantitative study

We will summarise the overall response rates of follow-up questionnaires categorised by the two intervention groups. Further missing data associated with each question within the questionnaire will be summarised by intervention group. Over all the rates of attrition will be summarised by group.

*5.2.4.2* Nested qualitative study

The qualitative evaluation will be carried out to examine the acceptability of the intervention as a whole package of care to both the trial participants and the podiatry practitioners. Trial participants receiving the intervention will be asked about their experience of receiving the intervention and how they felt this influenced the feasibility study outcome measures - particular attention will be paid to the acceptability and compliance with: the foot orthosis, exercise programme, podiatry service and footwear advice/purchase. We will ascertain from those in receipt of the intervention how this fits into the individual’s wider experience of balance problems within their every day lives. For example, how the intervention fits with their understanding about the reasons for falling, fear of falling, its impact on their life and how they cope with this. We will also ask trial participants more generally about the trial process itself, for example the acceptability of the randomisation procedure and the methods of data collection. This will take the form of established methods for qualitative process evaluation of trials as developed by Donovan et al. [28]

Fifteen trial participants will be purposively selected from the pilot trial. This sample will include 10 participants from the intervention arm and 5 from the control arm and will ensure a maximum variation spread according to age and gender. All participants will be invited to attend a face-to-face interview at a location convenient for them, in order to enhance the rapport between the researcher and the participant and facilitate data collection. However, if the participant preferes the interveiw may be conducted over the phone. The researcher will obtain informed consent from the participant prior to the interview being conducted. The semi-structured interviews will be conducted within approximately two weeks of receiving the 6 month follow-up questionnnaire. All interviews will be conducted using a topic guide to ensure consistency across participants, however, the format will be flexible in order to allow participants to generate naturalistic data on what they constitute as important and/or successful in terms of treatment outcomes and to take into account that only a proportion of the participants have received the intervention. Follow-up telephone interviews will be conducted with all respondents in the two weeks following the 12 month follow-up questionnaires. This will be to discuss any changes (or not) recorded in the outcomes measured over the longer term follow-up period.

We will interview all practitioners who are providing the podiatry services for the study (approximately 5) regarding the way in which they have delivered the intervention/control, the ease of delivery, their confidence in the intervention, and their experience of being involved in the trial. As for the interviews with trial participants, face-to-face or telephone interviews will be conducted using a topic guide and informed consent will be obtained prior to the interview being conducted. Interviews with practitioners will be conducted approximately 3 months into the trial process.

Withdrawal from the qualitative study can occur at any point at the request of the participant. Data will be retained for all participants up to the date of withdrawal, unless they specifically request their details to be removed.

*5.2.4.3 Qualitative analysis*

All interviews will be audio recorded digitally and transcribed verbatim. The computer package ATLAS-ti will be used to manage the data. Data will be analysed according to the constant comparison method through thematic coding of the data. [29] The coding will take place using a combination of a priori themes (according to the aims of the qualitative study and the outcome measures of interest to the trial) and emergent themes. The main focus of the analysis from the pilot phase would be to identify key issues that may inform the process of rolling out into the main trial. However, in addition, as participants in the qualitative sample would also have responses to the quantitative data collected for the feasibility trial, this will allow for the possibility of taking a mixed-methods approach to data integration, in which the two forms of data can be used to complementary way. [30]

**5.3 The REFORM Trial**

Upon successful completion of the pilot stage, the study will progress to a full pragmatic RCT with an economic evaluation.

5.3.1 Trial design

This is a two arm, pragmatic, open randomised cohort controlled trial with a 12 month follow-up.

5.3.2 Inclusion criteria

Participants will be eligible for the REFORM trial if they fulfil all of the following criteria:

1. The participant is 65 years of age and over
2. The participant has had one fall in the past 12 months; or one fall in the past 24 months requiring hospital attention.
3. They are community dwelling.
4. The participant reports a fear of falling i.e. worries about falling all of the time, most of the time, a good bit of the time, some of the time in the past 4 weeks i.e. on their baseline questionnaire.

5.3.3 Exclusion criteria

Participants will be excluded if they fulfil any of the following criteria:

1. The participant is known to have neuropathy.
2. The participant is known to have a neurodegenerative disorder.
3. The participant does not complete the baseline or run-in data collection instruments adequately ie fails to return baseline questionnaires.
4. Participant has had a lower limb amputation
5. The participant is unable to walk household distances (10 metres/32 feet) without the help of a walking aid such as a Zimmer frame or walker or person to assist. Patients who use a walking stick however, will be eligible for the study.
6. The participant is known to have dementia.
7. Participants are unable to read or speak English.

5.3.4. Primary outcome

The primary outcome is the rate of falls (i.e: falls/person/time) where a fall is defined as “an unexpected event in which the participant comes to rest on the ground, floor, or lower level”. [31]

5.3 5 Secondary outcome

Secondary outcomes are:

- Proportion of fallers
- Proportion of multiple fallers (more than two falls)
- Patient reported time to first fall during follow-up
- Health related quality of life as measured by the EQ-5D
- Short Falls Efficacy Scale
- Fear of falling
- Activity of Daily Living
- Fracture rate
- Health service utilisation
- Geriatric Depressions Scale

5.3.6 Sample size

This trial is designed to detect a 10% point reduction in the falls over 12 months. Assuming this high risk group have an underlying risk of 50% (the incidence observed in our recent trial of occupational Therapy for falls reduction) then in order to observe a reduction to 40% with 80% power and a two-sided 5% significance level would require 890 participants (445 in each group, allowing for a 10% loss to follow up). However, we propose to recruit 2,600 participants in to the REFORM cohort to allow us to sample for the feasibility phase and to allow cohort attrition before we sample for the main trial. If more than 890 participants are eligible for the REFORM trial we will recruit these and use unequal allocation, which will allow us to maintain the same size intervention group but increase the size of the control group and increase the power of the study.

5.3.7 Participant withdrawal

Participants can withdraw from the trial at any point by directly contacting the trial coordinator at the York Trials Unit or informing a member of the research team delivering the intervention. If a participant indicates they wish to withdraw from the study, withdrawal will be clarified as to whether the withdrawal is from the intervention only, from follow-up or all aspects of the study. Where withdrawal is only from the intervention then follow-up data will continue to be collected. The reason for the participant wishing to withdraw from the study will not have to be stated however; if the participant indicates the reason this will be recorded. Data will be retained for all participants up to the date of withdrawal, unless the participant specifically requests for their details to be removed.

5.3.8 Randomisation

Participants who fulfil the eligibility criteria and who have provided written consent to take part in the reform study will be eligible for randomisation into the REFORM trial. The randomisation will be carried out by the York Trials Unit Randomisation Service once all relevant data are collected and entered into the study database. Participants will be randomly allocated in a 1:1 ratio to either the intervention or control group. If more than 890 eligible participants are recruited then we will randomly allocate the remaining participants in a 2:1 ratio in favour of the control group. In order to allow for manageable case loads at individual sites, the randomisation will be blocked and stratified by centre with the allocation sequence being computer generated. Participants will be randomised in batches, the frequency of which will be determined by the capacity of the site delivering the intervention. The York Trials Unit (YTU) will write to participants and their GP’s informing them about their group allocation. The podiatrists delivering the intervention will be notified that a new participant has been randomised to the intervention group via email, telephone call or letter. The podiatrist will then access a secure website to retrieve details of the participant and will arrange the required appointments for that participant.

5.3.9 Blinding

Blinding of the participants will not be feasible, nor is blinding of members of the study team who are actively involved in the administration of the study, or the health economist. However, members of study team responsible for the statistical analysis of the study will be kept blind to group allocation.

5.3.10 Intervention group

The intervention group will be seen by the podiatrist as soon as possible after randomisation for an initial visit to assess their foot health. They will receive a multifaceted foot and lower limb intervention. This type of ‘technology’ represents a ‘complex healthcare intervention’ and this study, therefore is informed by the stepwise MRC complex interventions framework. [32] As a result, the pilot trial will address the acceptability and compliance of the complex intervention as a whole package. The multifaceted foot and lower limb intervention will consist of:

1. Footwear advice and provision (where indicated following footwear assessment.)

Participants’ everyday footwear will be assessed using a footwear assessment form which will record the following shoe characteristics; appropriate size; method of fastening; height and width of the shoe’s heel; thickness of outsole; heel counter stiffness, longitudinal sole rigidity; sole flexion point; tread pattern. Footwear will be deemed to be inappropriate if the shoes have any of the following characteristics:

- The heel height is greater than 4.5cm
- No fixation
- No heel counter or the heel counter can be depressed to greater than 45o
- A fully worn/smooth/thin sole
- The shoe heel width is narrower than the participant’s heel width by greater than or equal to 20%
- Incorrect shoe size

Participants with inappropriate footwear will be counselled regarding the specific hazardous footwear feature(s) identified during the assessment. The participant will then be advised to purchase a more appropriate pair of shoes. In order to allow participants to do this, they will be given an £80 voucher. This voucher will be redeemable at shoe shops participating in the Healthy Footwear Guide (HFG) Scheme [33] (Current manufacturers participating in the scheme as of March 2011 are: Clarks, DB Shoes, Healthy Feet at [**www.healthyfeet.co.uk**](http://www.healthyfeet.co.uk/), Padders, Simply feet and Websters shoes.) or other shoe shop which the local podiatry clinic would routinely advise patients to purchase shoes from, so this will eliminate the possibility of the participant purchasing non-ideal footwear with the voucher. Alternatively the podiatrists or a member of the research team may order shoes directly from the company. In order to avoid incentivising patients to take part in the study, participants will only be told about the voucher if they are deemed to need new footwear. Recruiting sites who employ a designated ‘shoe fitter’ as part of their routine podiatry service will be asked to accompany patients whilst purchasing new shoes and give advice about the suitability of footwear.

1. Routine podiatry care

Routine podiatry care will be given at a separate Podiatry appointment which will aim to reduce painful conditions, particularly corns and callouses, that has been found to be associated with an increase risk of falls.

1. Foot orthoses:

Participants will be fitted with a prefabricated insole. The type of insole fitted will be determined by the results of the pilot trial and will be either a (Formthotics TM Foot Science) or an x-line. The orthoses will then be appropriately customised using appropriate self-adhesive additions to improve the foot posture The orthosis will be supplied either by the podiatrist delivering the intervention or by a manufacturer in response to a prescription from the podiatrist.

1. Home based foot and ankle exercise programme

Participants will be prescribed a 30 minute home based foot and ankle exercise programme which should be undertaken three times per week indefinitely. The exercises will be demonstrated by the podiatrist at the participant’s initial visit and will be supplemented by a DVD demonstrating the exercises and an illustrated explanatory booklet showing how to do them at home. The exercise programme which is aimed at stretching and strengthening the muscles of the foot and ankle is based on the programme developed by Spink MJ *et al [22]* and the routine exercises prescribed by podiatrists in the UK.

Participants will complete a questionnaire at 1, 3, 6 and 12 months after randomisation to collect data on compliance with the intervention including the exercise programme footwear advice and insole use, which will be returned to the YTU.

1. Falls prevention leaflet

Participants will receive a copy of the latest falls prevention advice leaflet produced by Age UK. The current version of this document is called “Staying steady. Improving your strength and balance”. This leaflet will be sent to the participant in the post with their baseline questionnaire.

Participants will be sent a site and group specific newsletter at three months and with their six month follow-up questionnaire to inform them about progress with the study. The intervention group’s newsletter will include a section about the foot and ankle exercises in order to aid compliance.

The podiatrist will book a second appointment in approximately two to four weeks time to allow participants sufficient time to purchase new shoes if required. At the second appointment the podiatrist will check the suitability of the new footwear, check that the orthotic device is fitted correctly, customising if necessary. The podiatrist will reinforce the exercise programme. They will ask the participant if they have experienced any adverse events since their last appointment and if they have experienced any problems after undertaking the exercise programme.

It is not anticipated that participants will require a third appointment, however, if participants experience any problems with their orthotic, they will contact the clinic directly to arrange further appointments as required.

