5.3.11 Control group

Participants in the control group will receive the same leaflet as the intervention group which will give falls prevention advice. This leaflet will be sent to the participant in the post with their baseline questionnaire. Participants will continue whatever podiatry treatment they currently receive for the 12 months of the study and usual GP care.

Participants will be sent a site and group specific newsletter at three months and with their six month follow-up questionnaire to inform them about progress with the study.

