Hospitalisations, disabling / incapacitating / life-threatening conditions, falls and deaths are expected in the study population due to the age of the cohort, they will therefore only be reported as SAEs if they appear to be related to an aspect of taking part in the study. Expected adverse events which are related to the intervention include: aches and pains in the lower limb for longer than 48 hours; fall; new callus/corn formation, blisters, ulcers; skin irritation/injury including pressure sores; soft tissue injury. If a participant or a member of the research team rings the York Trials Unit to notify the occurrence of an adverse event, or an adverse event is reported in information provided in the follow-up questionnaires, then the trial coordinator – or designated person if unavailable should be informed immediately by telephone, email or in person. The trial coordinator (or designated person) will inform the Chief Investigator (CI) or designated person, and two members of the Trial Management Group (TMG) who will jointly decide if the event should be reported to the main REC as an SAE. Related and unexpected SAEs will be reported to the main REC within 15 days of the CI becoming aware of the event. Details of the assessment will be recorded on an ‘adverse event review form’.

The occurrence of adverse events during the trial will be monitored by an independent Data Monitoring Ethics Committee (DMEC)/ Trial Steering Committee (TSC). The DMEC/TSC will immediately see all SAEs thought to be treatment related and they will see SAEs not thought to be treatment related by the Trial Management Group at the next scheduled meeting.

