6.1 Site monitoring

Site monitoring visits for this study will not be undertaken on behalf of the sponsors since (a) eligibility for the study is undertaken by review of patient’s self-reported data sent to the York trials unit (b) the majority source data for this study is patient self-report questionnaires which is returned directly to the York Trials Unit and (c) data on adverse events will mainly be collected via patient self-reported data to the York Trials Unit. Participating sites will, however, be asked to assist in trial-related monitoring when required for example for audits, ethics committee review and regulatory inspections.

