**Intervention Group**

**N = 445**

**Control Group**

**N = 445**

Baseline data

Falls prevention advice

Routine podiatry

Orthotic assessment

Footwear advice

Foot and ankle exercises

Baseline data

Falls prevention advice

6 month follow-up

12 month follow-up

6 month follow-up

12 month follow-up

Clinical review

Orthotic fitting

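### The only prompted adverse-event enquiry the protocol describes comes early and in the intervention arm alone, so non-fall harms are ascertained unequally between the arms

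*Protocol*

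**What the plan says.** Section 5.3.10 sets the timing of the second visit: "The podiatrist will book a second appointment in approximately two to four weeks time". At that visit the podiatrist enquires about harms: "They will ask the participant if they have experienced any adverse events since their last appointment". No later trial visit is planned: "It is not anticipated that participants will require a third appointment". After that, contact with the clinic is at the participant's initiative.

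The control arm has no trial appointment. Section 5.3.11 provides a leaflet and newsletters, and otherwise: "Participants will continue whatever podiatry treatment they currently receive for the 12 months of the study and usual GP care".

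Section 5.3.13 lists the expected intervention-related events. Apart from falls and lower-limb aches lasting more than 48 hours, they are "new callus/corn formation, blisters, ulcers; skin irritation/injury including pressure sores; soft tissue injury". It also gives two reporting routes that do not depend on arm: a telephone call to the trials unit, "or an adverse event is reported in information provided in the follow-up questionnaires". Section 6.1 makes self-report the principal source: "data on adverse events will mainly be collected via patient self-reported data to the York Trials Unit". It gives this as one of its reasons for having no site monitoring visits.

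Appendix 3, the data collection schedule, has no adverse-event row. Its nearest item, foot problems, is ticked at baseline only and marked as intervention group only.

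**The concern.** The insole and the exercise programme are used well beyond the first month. Exercise is prescribed three times a week with no end date (5.3.10), and orthotic use is tracked to 12 months (5.4.7). The described enquiry ends at the second visit, so a skin or soft tissue problem arising in month 5 is known only if the participant reports it.

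The second problem is comparability. One arm is asked face to face by a clinician and the other is not. The oversight committee is to monitor the occurrence of adverse events (5.3.13), and its independent members may see unblinded data (section 9, Independent Steering Committee). A by-arm listing of these harms would then reflect how events were sought as well as how often they occurred. A statistical analysis plan cannot repair this, because it cannot recover events nobody asked about.

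**Working it through.** The protocol gives no numerical figure for harms, and its sample size plays no part here. The check is a comparison of sources by arm, plus one proportion.

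**Share of follow-up covered by the prompted enquiry.** Inputs: a second visit two to four weeks after the first (5.3.10) and 12 months, or 52 weeks, of follow-up (5.3.1).
- Two weeks: 2/52 = 3.8%.
- Four weeks: 4/52 = 7.7%.
- Remainder with no described prompt in the intervention arm: 1 - 0.077 = 92.3% to 1 - 0.038 = 96.2%.
- Control arm: 100% with no described prompt.

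Appendix 3 heads the same visit 2/3 weeks, so the two statements of timing should be reconciled. At three weeks the share is 3/52 = 5.8%, inside the range above.

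**Sources by arm.**

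| Source | Intervention | Control |
| --- | --- | --- |
| Podiatrist asks about adverse events (5.3.10) | Once, at 2-4 weeks | None described |
| 1- and 3-month compliance contact (Appendix 3) | Yes | No (marked intervention only) |
| Telephone or questionnaire report (5.3.13) | 12 months | 12 months |
| Falls and fall injuries (5.4.2) | Calendars, telephone chase, questionnaire back-up | Same |
| Fractures (5.4.6) | 6 and 12 months | Same |

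For falls, fall injuries and fractures the described sources match. For the other named harms, the only shared route is one for which no prompt is described.

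**Direction of the bias.** Let *w* be the share of intervention-arm events that fall before the second visit, *e* the fraction of events captured when prompted, and *s* the fraction captured when not. Assume *s* is the same in both arms.
- Captured fraction, intervention: *we* + (1 - *w*)*s*.
- Captured fraction, control: *s*.
- The observed event ratio equals the true ratio multiplied by 1 + *w*(*e*/*s* - 1).

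The multiplier exceeds 1 whenever *w* > 0 and *e* > *s*, so the distortion is towards more events in the intervention arm. The documents give none of *w*, *e* and *s*, so no value can be put on it.

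**Whether the answers are kept.** Section 5.3.13 first says that details of any adverse event reported to the trials unit go on a form. It then says that non-serious events are neither recorded nor reported. Most of the named harms would usually be non-serious, so the answers obtained at the second visit have no clear place to go.

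**The case against.** The strongest objection is that this rests partly on silence. The follow-up questionnaires are not shown, and 5.3.13 expects adverse events to appear in them. They may carry a direct question, put to both arms at 6 and 12 months. Nor does Appendix 3 settle it: it has no adverse-event item at the second visit either, although 5.3.10 says the question is asked there. This stands, and it limits the claim to what the protocol describes. A reader might infer that nobody asks again after week 4, or that later harms are invisible; the documents do not show that.

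Next, the analysis sections (5.4.4 to 5.4.7) plan no between-arm comparison of adverse events, and the rule against recording non-serious events would leave little to compare. That also stands in part: the bias applies to any such count that is made. But 5.3.13 contradicts itself on recording and gives the oversight committee a monitoring role, so a by-arm count is not far-fetched.

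There are other safeguards. Participants with orthotic problems can contact the clinic, extra trial appointments generate extra data, and control participants' podiatry attendance and treatment are recorded (5.4.1). The first two serve the intervention arm and so do not restore balance. The third is a record of service use, not an enquiry about harm.

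Three stronger readings are tempting and unsupported:
- **Biased fall reporting.** Because falls are on the expected-event list, a reader might infer that the podiatrist's question inflates falls in one arm. Both arms have daily calendars, a telephone chase and questionnaires (5.4.2), and the podiatry visit is not among the fall sources in 5.4.2 or 5.4.6.
- **A numerical bias ratio.** Any figure would come from assumed capture rates, not from the documents.
- **Enquiry before exposure.** The main-trial flow chart in Appendix 1 lists "Orthotic fitting" near the clinical review, so a reader might think the question precedes insole use. The chart's layout is lost in the text available here. Section 5.3.10 has the second visit checking a fitted device, and Appendix 3 places orthotic prescription at baseline.

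**Conclusion.** The point holds for the non-fall harms only. As described, prompted ascertainment covers roughly 4-8% of follow-up in the intervention arm and none in the control arm. Later events rely on unprompted self-report in both arms, unless the unseen questionnaires ask about them. A by-arm count that pooled these sources would lean towards more events in the intervention arm. That conclusion assumes that asking finds more events than not asking and that unprompted reporting is similar in the two arms. The size of the bias is unknown.

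This is a moderate weakness in the collection of harms data, in a trial the protocol regards as low risk. It does not touch the primary outcome or fractures. It is worth correcting because the remedy is cheap and must be in place before the data are collected.

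**What to change.** 1. Add the non-fall events named in 5.3.13, together with hospital admission, as identically worded items on the 6- and 12-month questionnaires already sent to both arms. Add the corresponding row to Appendix 3. If the questionnaires already contain such items, say so in 5.3.13 and add the row. The 1- and 3-month compliance contacts are unsuitable for a common item because they go to one arm.
2. State that any between-arm comparison of adverse events uses only sources common to both arms. List events elicited by the podiatrist separately, as intervention-arm data.
3. Reconcile the two statements in 5.3.13 on recording, so that it is clear which reported events are kept and the answers to the new items are not discarded. Without this, the first step achieves nothing.
4. Reconcile the timing of the second visit between 5.3.10 and Appendix 3.

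The cost is a few tick-boxes on two existing questionnaires, a wording amendment, and more events for the trials unit to review.
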